### Statistical aspects

#### Sample size calculation

The DIPLOMA-2 trial is designed as a non-inferiority trial, hypothesizing that the mean CCI® score of MIPD is non-inferior to OPD. Calculations are based on results of the pan-European E-MIPS retrospective cohort study and on individual patient-data collected from the previous conducted RCTs on MIPD versus OPD. The sample size is calculated using PASS 2022 software to achieve 80% power (1-β) in a per-protocol analysis with the following assumptions: 2.5% one-sided significance level (α), expected difference of the mean CCI® score in the MIPD and OPD group of 0 points, and a non-inferiority margin of 7.5 points, standard deviation of 20 points in both groups, including 5% metastasized disease, a 10% conversion rate and a 3% lost-to-follow-up rate after randomization leads to a total number of patients to be randomized of 288 (192 in the MIPD study arm and 96 in the OPD study arm). For time to functional recovery, we assume MIPD will result in a reduction of 2 days (7 days in the MIPD group versus 9 days in the OPD group. Time to functional recovery will be measured in days and will be tested for superiority using the Wilcoxon (Gehan-Breslow) test or the log-rank test (based on non-normal distribution). With a one-sided testing, assuming 5% metastatic disease, 10% conversion rate, and 3% loss to follow-up, a sample of 247 patients (159 in the MIPD group and 88 in the OPD group) in a per protocol analysis achieves 80% power to detect a 28% reduction of time to functional recovery (i.e., 6.5 days in the MIPD group; hazard ratio = 0.72). The estimated median time to functional recovery of 9 days in the OPD group is based on results of the LEOPARD-2 trial and corresponds to a median TTFR reduction of 2.5 days.

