The primary outcome measure “CCI®” will be expressed as means (standard deviations) or medians (interquartile ranges) and will be tested for non-inferiority using independent samples *t*-test or Mann–Whitney *U* test, as appropriate dependent of the distribution. The most important secondary outcome measure “time to functional recovery” will be measured in days and will be tested for superiority using the Wilcoxon (Gehan-Breslow) test or log-rank test, depending on the distribution. Secondary analysis will include correction for censored patients (death before time to functional recovery obtained). For the primary study outcome, the lower limit of the two-sided 95% confidence interval of the difference in proportions will be reported and compared with the non-inferiority margin. Additionally, the individual functional recovery criteria will be analyzed separately. Major complications, expressed in proportions, will be tested for non-inferiority using chi-square or Fisher’s exact test as appropriate. The distribution of variables will be determined using several plots (boxplot, Q-Q plot and histogram) and the Kolmogorov–Smirnov and Shapiro–Wilk tests. For comparison of normally distributed continuous variables, the independent samples *t*-test will be used, and values will be expressed as means (standard deviations). Continuous non-normally distributed variables will be compared using the Mann–Whitney *U* test, and values will be expressed as medians (interquartile ranges). Categorical variables will be compared by chi-square or Fisher’s exact test as appropriate, and values will be expressed as proportions. A two-tailed *p*-value < 0.05 will be considered statistically significant. Time to event endpoints, such as survival, will be calculated using Kaplan–Meier estimations. A Cox regression analysis will be performed to investigate predictors of postoperative survival. All parameters with a *p*-value < 0.1 in a univariable analysis will be included in the multivariable Cox regression analysis. Additionally, multivariable analyses will be performed to determine predictors for primary and secondary study outcomes, for example the occurrence of major complications, postoperative pancreatic fistula, and R0 resection. Furthermore, predictors for receiving adjuvant chemotherapy or readmission will be assessed.

For subjects who are lost to follow-up, a sensitivity analysis will be performed to determine best case/worst case scenarios.

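### The survival Cox model picks its covariates by univariable p < 0.1, which inflates the effects it keeps and leaves allocation and the randomisation factors unprotected

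*Protocol article*

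**What the plan says.** The Statistical analysis section of the protocol article announces a survival model in these terms: "A Cox regression analysis will be performed to investigate predictors of postoperative survival". It then fixes the entry rule: all parameters with p < 0.1 "in a univariable analysis will be included in the multivariable Cox regression analysis". It names no candidate list and does not say that allocation or the stratification factors stay in the model whatever their p-value. The Randomization section gives those factors as minimally invasive technique, preoperative fistula risk, and indication (PDAC or other).

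The section goes on to say that "multivariable analyses will be performed to determine predictors for primary and secondary study outcomes", with major complications, pancreatic fistula and R0 resection as examples, and that predictors of adjuvant chemotherapy and of readmission will be assessed. It states no selection rule for any of these.

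The treatment comparisons are set out separately. CCI "will be tested for non-inferiority using independent samples" t-test or Mann–Whitney test, time to functional recovery is compared by a Gehan-Breslow or log-rank test, major complications by chi-square or Fisher's exact test, and survival is estimated by Kaplan–Meier. A detailed SAP is promised before lock of the 90-day data.

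**The concern.** Univariable screening uses the outcome data to choose the covariates and then reports the final model as if no choice had been made. An estimate that enters only when it is large enough to pass a threshold is, on average, too large. A noise variable that enters has by construction an extreme estimate, so its interval tends to miss the truth. A real but weak predictor is often lost.

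A rule that applies to all parameters also carries no exception for allocation, or for factors that the design itself treats as prognostic. PDAC versus other indication is the clearest example in a survival model.

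At stake is a planned analysis of a listed secondary outcome with follow-up to 36 months: the published hazard ratios and intervals for predictors of survival, and any adjusted treatment estimate read from the same model.

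**Working it through.** **What can be reproduced.** The article gives no figure for this model: no number of candidates, no expected deaths, no effect sizes. Its sample size figures do reproduce. Attrition gives 192 × 0.95 × 0.90 × 0.97 = 159.2 and 96 × 0.95 × 0.97 = 88.5, matching the stated 159 and 88. With margin 7.5 and SD 20 ("a non-inferiority margin of 7.5 points, standard deviation of 20 points in both groups"), SE = 20 × √(1/159 + 1/88) = 2.657, and power = Φ(7.5/2.657 − 1.96) = Φ(0.862) = 80.6%, against the stated 80%. That calculation contains no covariate selection, so the screen does not touch it.

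**Inputs.**
- From the article: entry at p < 0.1; general two-sided 0.05 level; 2:1 allocation; 257 patients operated on at submission (Trial status).
- Assumed: about 146 deaths, or a range of 100 to 200; 15 or 25 independent, standardised candidates; 0 or 3 true predictors with log hazard ratio 0.15 or 0.20 per SD.

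**1. Noise variables that pass.** Of k null candidates, 0.1k pass on average. At the 5% level about 0.05/0.10 = 50% of those are significant, and their 95% intervals miss zero equally often. Cox simulation (2,000 to 3,000 runs per setting) gave 46% to 51% significant and coverage of 49% to 54%. A repeat with about 145 to 160 deaths gave coverage of 53% to 57%. Average coverage over all candidates in an unscreened full model was 93% to 94%.

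**2. True predictors that pass.** SE ≈ 1/√146 = 0.083, so the estimate must exceed about 1.645 × 0.083 = 0.136 in absolute value. With a = (0.136 − β)/0.083, the mean estimate given passing is β + SE × φ(a)/[1 − Φ(a)], ignoring the negligible opposite tail.

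| True log HR | Passes (formula) | Mean if kept (formula) | Passes (simulated) | Mean if kept (simulated) |
|---|---|---|---|---|
| 0.15 | 0.57 | 0.21 | 0.54 to 0.55 | 0.21 |
| 0.20 | 0.78 | 0.23 | 0.75 | 0.235 |

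So 25% of true predictors at 0.20 and 45% to 46% at 0.15 are dropped in simulation. Interval coverage for kept true predictors stayed at about 95% to 96%: for them the problem is bias away from zero, not width.

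**3. Allocation, if it is screened.** With D deaths and 2:1 allocation, z = |log HR| × √(D × 2/3 × 1/3), and P(dropped) = Φ(1.645 − z) − Φ(−1.645 − z). Example: D = 150, HR 0.8 gives z = 0.223 × √33.3 = 1.288 and P = Φ(0.357) − Φ(−2.933) = 0.64.

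| Deaths | HR 0.9 | HR 0.8 | HR 0.7 |
|---|---|---|---|
| 100 | 0.86 | 0.72 | 0.49 |
| 150 | 0.84 | 0.64 | 0.34 |
| 200 | 0.82 | 0.56 | 0.23 |

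At HR 1.0 the probability is 0.90 by definition of the threshold.

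**4. Does the screen create more false predictors?** With 15 null candidates, at least one is falsely significant by chance with probability 1 − 0.95^15 = 54%. Simulation gave 53% with the screen and 59% in the full model. With 3 true predictors at 0.20 among the 15, it gave 43% and 53%. So the screen does not raise this count.

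**The case against.** The strongest reply is that this is one exploratory model of survival predictors, that no treatment conclusion depends on it, and that candidate lists and forced terms belong in the SAP. Much of that stands. CCI, time to functional recovery and major complications are compared by two-group tests that never meet the screen, and the conclusions the article sets out to draw concern CCI and functional recovery. An unnamed candidate list is not in itself a fault in an article. The selection rule, however, is not left to the SAP: the article states it.

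Three stronger readings are tempting, and the document does not support them.
- A reader might infer that the p < 0.1 rule governs all the predictor models, including fistula and R0 resection. It is written only for the Cox regression; the others have no stated rule.
- A reader might infer that screening multiplies false predictors. The roughly even chance of at least one comes from testing many candidates, and an unscreened model with the same candidates does no better.
- A reader might infer that the treatment effect will be lost. The article does not say that allocation is a candidate in this model, and the model's stated purpose is to find predictors. Loss of the term is possible under the wording, not shown, and would touch only an adjusted survival estimate.

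**Conclusion.** The point holds for the survival Cox model alone, and it is minor. The stated rule pushes the weak effects it keeps away from zero by roughly a fifth to two fifths on the log scale (0.20 to 0.235; 0.15 to 0.21). It drops a quarter or more of such predictors and gives intervals that fail about half the time for the noise variables it admits. It offers no protection to allocation or to the stratification factors.

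The sizes rest on assumed deaths, candidate numbers and effect sizes, and on independent covariates, because the document gives none of these. The direction of the bias does not depend on them: it follows from selecting on the same data that are then used for estimation.

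**What to change.** In the SAP, replace the p < 0.1 screen for the survival Cox model with a covariate list fixed in advance on clinical grounds and sized to the expected number of deaths. Always include allocation and the three stratification factors (technique, fistula risk, PDAC or other indication). Fit the full model, with penalisation if deaths are few, and label it exploratory. Do not carry the screen over to the models for major complications, fistula, R0 resection, adjuvant chemotherapy or readmission. Keep the list short: only fewer candidates, not the removal of the screen, will lower the number of false predictors.

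The change needs no new data and no change to the design. It costs SAP wording, agreement on the list before the survival data are analysed, and somewhat wider intervals.

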### Randomization

Patient recruitment and the collection of written informed consent are performed at the outpatient clinic. Hereafter, all patients will be randomized centrally by the study coordinators using an online computer controlled permuted-block randomization module (Castor EDC, CIWIT B.V., Amsterdam, the Netherlands). Randomization between MIPD and OPD will be performed in a 2:1 ratio, with block sizes varying between 3, 6, and 9 patients. The entire randomization process will be concealed to all involved investigators, except the study coordinator. Randomization will be stratified for the minimally invasive technique (laparoscopic or robotic), the pre-operative risk of post-operative pancreatic fistula (normal versus high risk, based on BMI (< 25 kg/m^2^ and ≥ 25 kg/m^2^) and pancreatic duct diameter (< 3 mm or ≥ 3 mm) on pre-operative imaging), and for the indication (pancreatic ductal adenocarcinoma (PDAC) or other indication). Patients will be coded by a numeric randomization code, and the study coordinator will be the only one with access to it. The source data will be stored digitally and will be kept by the project leader for 15 years after the last patient’s follow-up is completed.

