### Primary outcome

The primary outcome is the Comprehensive Complication Index (CCI®), measured up to 90 days post-operatively. The CCI® score is developed to reflect the postoperative morbidity based on the Clavien-Dindo classification of postoperative complications and is validated for pancreatic surgery [23–25]. The CCI® score ranges from 0 (no complication of any kind during the postoperative period) and 100 (death of patient). The advantage of the CCI® over the Clavien-Dindo classification is the ability to accumulatively assess the postoperative morbidity considering all complications instead of only scoring the “most severe” complication. Repeat Clavien-Dindo 1 complications will be counted only once (i.e., not be scored cumulatively) in the CCI.

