### Secondary outcomes

The most important secondary outcome is postoperative time to functional recovery. Functional recovery, as defined by a previous RCT [19, 20], is reached when all of the following criteria are met: (I) adequate pain control with oral analgesia only; (II) restoration of mobility to an independent level (or to preoperative level if previously impaired); (III) ability to maintain sufficient caloric intake (minimum of 50% required calories); (IV) absence of intravenous fluid administration; (V) no signs of active infection (no fever, decreasing C-reactive protein below 150 mg/L).

Post-operative activity will be measured using a Fitbit™ Inspire 2, by patients on their wrists (1–2 weeks) from prior to surgery to 90 days after surgery [26–29]. A comprehensive overview of the outcomes of the postoperative activity tracking will be described as a separate publication.

Other secondary outcomes of this trial include intra-operative parameters (type of surgery (laparoscopic or robot-assisted), conversion (urgent or non-urgent), method of anastomosis, vessel resection, operative time, blood loss, and blood transfusion), postoperative outcomes (up to 90 days after surgery; major complications (defined as a Clavien-Dindo grade III or higher) and mortality (and whether related to surgery), postoperative pancreatic fistula [30], post-pancreatectomy hemorrhage [31], delayed gastric emptying [32], chyle leak [33], surgical site infection [34], postoperative intervention (surgical, radiologic or endoscopic), intensive care unit admission, (multi) organ failure, length of hospital stay, readmission, (time to) start of adjuvant therapy) and pathological outcomes (pathological diagnosis, tumor size, histology and tumor grading [35], distance from the tumor to all margins, number of retrieved lymph nodes, number of positive lymph nodes, lymphovascular and perineural tumor invasion, and venous and arterial tumor involvement). For the economical evaluation, costs (intra-operative and postoperative costs (up to 90 days)) and quality of life (using the validated EQ-5D-5L, QLQ-C30, and PAN-26 questionnaires with additional questions regarding scar complications and body image (up to 3 years)) are compared [36, 37].

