### Quality and safety

A minimum annual center volume of at least 30 MIPD and 30 OPDs was set as requirement for participating in the DIPLOMA-2 trial. By using this volume requirement, we aim for centers to maintain an annual volume of at least 20 MIPD during the trial, despite randomization [14]. Centers will participate for either L-MIPD or R-MIPD, depending on their main expertise. Surgeons are allowed to participate in DIPLOMA-2 if they have a personal experience of at least 60 MIPDs and 60 OPDs in the past 10 years.

All MIPD surgeons will be required to have participated in an endorsed MIPD training program or otherwise are asked to send a recorded and anonymized video of a personal MIPD procedure performed, before the start of the trial, which will be evaluated by the study team. In addition, the MIPD procedures within the DIPLOMA-2 trial will be recorded and stored, to be available upon request of the study team.

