The following pre-specified subgroup and sensitivity-analyses will be performed:Comparing MIPD and OPD in patients with major complications (Clavien-Dindo grade ≥ III) and without major complications (no complication or Clavien-Dindo I-II) separatelyComparing centers for low and high annual MIPD volume during the trial separately (< 20 MIPD/year versus ≥ 20 MIPDs/year)Comparing MIPD and OPD in patients with pre-malignant indications and PDAC separately.Comparing incidence of POPF in MIPD and OPD for the ISGPS subgroups of POPF risk and the A-B-C variant [39, 40].oA—not soft (hard) texture and MPD > 3 mmoB—not-soft (hard texture and MPD ≤ 3 mmoC—soft texture and MPD > 3 mmoD—soft texture and MPD ≤ 3 mmComparing R-MIPD and OPD for the primary outcome CCI®, time to functional recovery, and other outcomesComparing L-MIPD and OPD for the primary outcome CCI®, time to functional recovery, and other outcomesComparing R-MIPD and L-MIPD for the primary outcome CCI and time to functional recovery 

A detailed statistical analysis plan will be drafted prior to database lock of the short-term outcomes (up to 90 days postoperative). Despite all prior preventive measures taken, a complex international trial may evoke unforeseen situations after database lock that threaten data integrity and can only be resolved by unlocking the database prior to the final analysis. For purpose of transparency and reproducibility, the statistical analysis plan will therefore also describe the procedure to be followed when such situations arise.

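### A planned subgroup splits the arms by major complication, a post-randomisation outcome; robotic versus laparoscopic is a between-centre contrast; and the open comparator for each technique is not defined

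*Protocol article*

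**What the plan says.** The Statistical analysis section lists pre-specified subgroup and sensitivity analyses. Two groups of entries matter here.

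- **Split by complication.** The list has "Comparing MIPD and OPD in patients with major complications" (Clavien-Dindo grade III or above) and, separately, in patients with none or only grades I-II. No outcome is named for this entry.
- **Technique.** There are three contrasts: R-MIPD against OPD, L-MIPD against OPD, and "R-MIPD and L-MIPD for the primary outcome CCI and time to functional recovery".

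Other sections show what these variables are.

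- Secondary outcomes lists, among results up to 90 days, "major complications (defined as a Clavien-Dindo grade III or higher").
- Statistical analysis adds: "Major complications, expressed in proportions, will be tested for non-inferiority".
- Primary outcome says that the CCI was developed to "reflect the postoperative morbidity based on the Clavien-Dindo classification of postoperative complications".
- Quality and safety states: "Centers will participate for either L-MIPD or R-MIPD, depending on their main expertise".
- Randomization makes the minimally invasive technique a stratification factor for the 2:1 MIPD:OPD allocation.

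**The concern.** A subgroup analysis keeps the protection of randomisation only if the subgroup is fixed before treatment can affect it. Whether a patient has a major complication is a result of the operation, and it is part of the safety question the trial asks. If MIPD raises or lowers that rate, the patients with a major complication in one arm are a different selection from those in the other, and so are the patients without. The difference within each stratum then mixes treatment effect with selection. It also leaves out the part of the effect that consists of moving patients from one stratum to the other.

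The technique contrasts raise a different question. Technique goes with centre, so robotic against laparoscopic compares two sets of hospitals. Each technique against OPD does have randomised controls, but only the OPD patients allocated in the same technique stratum. Pooling all OPD patients would bring the between-centre difference back in.

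At stake are secondary analyses that the plan lists on an equal footing, with no statement that some of them are not randomised comparisons.

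**Working it through.** **Confirming the inputs.** No stated figure is in dispute. The inputs from Sample size calculation are margin 7.5, SD 20, one-sided 2.5% and 80% power. Attrition is 5% metastatic disease, 10% conversion and 3% loss to follow-up. With conversion applied to MIPD only, 192 × 0.95 × 0.97 × 0.90 = 159 and 96 × 0.95 × 0.97 = 88. The t-test power is then 80.3%, so 288 is reproduced.

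**1. Split by major complication.** The article gives no CCI distribution. Assumptions: OPD CCI is gamma (shape 1.6, scale 16) clipped to 0-100, with SD about 20. CCI of 33.7 or more stands in for a major complication. There are 2,000,000 draws per arm. Two forms of harm were tried: additive (+7.5 for every MIPD patient) and proportional (scale × 1.3).

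| Harm | Overall difference | Major share, MIPD vs OPD | Difference in major | Difference in no major |
|---|---|---|---|---|
| Additive | 7.4 | 38% vs 27% | 0.4 | 4.8 |
| Proportional | 7.2 | 39% vs 27% | 5.2 | 1.1 |

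In neither row can an average of the two stratum differences reach the overall one. Weighted by the OPD shares:

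- Additive: 0.27 × 0.4 + 0.73 × 4.8 = 3.6, so 7.4 − 3.6 = 3.8 points are missing.
- Proportional: 0.27 × 5.2 + 0.73 × 1.1 = 2.2, so 7.2 − 2.2 = 5.0 points are missing.

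The missing part is the movement of patients into the major stratum. Moving the cut to 26.2 or 40 under additive harm gives 0.7 and 4.3, or about 0.3 and 5.2.

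A second model used latent severity with half its variance from baseline frailty and an OPD major-complication rate of 30-50%. A true difference of 5 points, in either direction, shrank to 1.2-2.0 points among patients with a major complication and 1.7-2.6 among those without. Baseline frailty differed between arms by 0.08-0.13 SD within strata. With no treatment effect there was no distortion.

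**2. R-MIPD against L-MIPD.** A baseline CCI difference D between robotic and laparoscopic centres passes in full into this contrast. Chance differences between centres also matter. Assume 14 centres split 7/7, 96 MIPD patients per technique, no true difference, and a two-sided 5% test that ignores centre. The true variance exceeds the one used by the factor V = 96 × ICC/7 + (1 − ICC), and the error rate is 2 × [1 − Φ(1.96/√V)].

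| ICC (assumed) | V | Error rate, formula | Error rate, 20,000 simulations |
|---|---|---|---|
| 0.01 | 1.13 | 6.5% | 6.6% |
| 0.02 | 1.25 | 8.0% | 8.4% |
| 0.05 | 1.64 | 12.5% | 12.3% |
| 0.10 | 2.27 | 19.3% | 19.5% |

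**3. Each technique against OPD.** Let r be the robotic share, and let robotic centres have baseline CCI higher by D in both arms. Pooled OPD then lies rD above the laparoscopic level. With no treatment effect:

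- R-MIPD against pooled OPD: D − rD = D(1 − r).
- L-MIPD against pooled OPD: 0 − rD = −rD.
- Either technique against OPD of its own stratum: 0.

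With D = 5 and r = 0.7 (both assumed), the biases are 5 × 0.3 = 1.5 points and −5 × 0.7 = −3.5 points.

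**The case against.** The strongest reply has five parts.

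- **These are subgroup and sensitivity analyses.** The overall CCI is the primary test, and the proportion with major complications is tested separately, so a rise such as 27% to 38% would show there. This stands, and it limits the consequence. It does not make the split a valid treatment comparison.
- **The entry names no outcome.** It may be meant for recovery time rather than CCI. This stands as a limit on the figures, which apply to CCI. The conditioning is on a post-randomisation event whichever outcome is analysed.
- **The size depends on the model.** It does. The additive model leaves no MIPD patient with a CCI below 7.5, which is unrealistic when 0 means no complication, and proportional harm reverses which stratum shows the larger difference. A reader might infer that the split would make a harmful operation look neutral in both strata. That is not shown: 4.8 of 7.4 points, or 5.2 of 7.2, is not neutral. Nor is 7.5 a yardstick for these strata, since that margin belongs to the primary test.
- **Technique is a stratification factor.** A reader might infer that every technique comparison is non-randomised. The Randomization section does not support this: R-MIPD and L-MIPD each have concurrent randomised OPD controls. Nothing says that OPD will be pooled, only that the comparator is not identified.
- **The rest is left to the analysis plan.** A reader might also fault the entry "Comparing MIPD and OPD in patients with pre-malignant indications and PDAC separately", because allocation is stratified "and for the indication (pancreatic ductal adenocarcinoma (PDAC) or other indication"), or fault the lack of interaction tests. A subgroup need not match a stratification factor, and interaction tests are commonly left to the analysis plan. Neither is an error here.

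**Conclusion.** The point holds in limited form. The major-complication split conditions on a post-randomisation outcome that is tested between arms and shares its grades with the primary CCI, so its contrasts are not randomised treatment effects. This follows from the text and needs no model. How far they mislead depends on whether MIPD changes the major-complication rate. With no effect there is no distortion. With a true difference of about 7 points, the assumed models give stratum differences between 0.4 and 5.2. The reliable finding is that both fall short of the overall effect, not the particular values.

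R-MIPD against L-MIPD is an observational comparison between centres. The error rates of about 6.5% to 19% rest on the assumed ICC of 0.01-0.10 and an even split of centres.

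R-MIPD and L-MIPD against OPD are sound randomised contrasts if OPD is confined to the same stratum. The defect there is only the unstated comparator. The primary test and the 288 patients are unaffected.

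**What to change.** Make three changes of wording, in the analysis plan that the article says will be drafted before database lock.

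1. Drop the major-complication split as a comparison of treatments, or label it descriptive. Report the distribution of Clavien-Dindo grades by arm.
2. State that R-MIPD and L-MIPD are each compared only with OPD patients randomised in the same technique stratum.
3. Label R-MIPD against L-MIPD as an observational comparison between centres.

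**Cost.** One planned subgroup comparison is lost, and the technique contrasts are less precise than with pooled OPD. With 70% robotic (assumed), SD 20 and all randomised patients, the standard errors are:

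- Robotic: 20 × √(1/134.4 + 1/67.2) = 2.99, against 20 × √(1/134.4 + 1/96) = 2.67 pooled.
- Laparoscopic: 20 × √(1/57.6 + 1/28.8) = 4.56, against 20 × √(1/57.6 + 1/96) = 3.33 pooled.

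If the 7.5-point margin were applied within a stratum, power would be 71% robotic and 37% laparoscopic at that share, 56% each at an even split, and 79% and 21% at 85% robotic. These contrasts should be read as estimates with intervals.
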